## Background

Urinary Tract Infections (UTI) are the most common bacterial infections requiring antibiotic treatment in the western world [1]. Complicated urinary tract infections (cUTI) are defined upon the presence of systemic symptoms or upon the susceptibility of the host for a complicated course [2]. Systemic symptoms are often fever, febrile UTI (FUTI), or other symptoms, reflecting the presence of tissue infection such as pyelonephritis, prostatitis or the urosepsis syndrome [2]. Guidelines recommend to treat FUTI with a 7–14 day course of antibiotics [2, 3] and in the majority of cases empiric intravenous antibiotics will be followed by oral stepdown therapy. The choice of stepdown treatment should be targeted to the susceptibility pattern of the causal uropathogen. Unfortunately, antibiotic options for stepdown treatment are becoming limited as the result of increasing antibiotic resistance [2].

*Escherichia coli* (*E.coli*) is the causative organism in around 70–75% of FUTI [4, 5]. In 2017, resistance rates of *E. coli* isolates of patients admitted to Dutch hospitals were 14% for ciprofloxacin (CPX), 23% for trimethoprim-sulfamethoxazole and 36% for amoxicillin-clavulanic acid with higher resistance rates in patients from urology departments [6]. Though this leaves fluoroquinolones still as one of the oral antibiotics to treat FUTI, one of the goals of antibiotic stewardship is to reduce fluoroquinolone use because of its selective properties for antibiotic resistance [2]. In the Netherlands, about 2–5% of patients hospitalized for community-acquired FUTI cannot be treated with oral antibiotics due to antibiotic resistance of the causal uropathogen [7]. This implies the need of prolonged intravenous antibiotic treatment, prolonged hospitalization, increased healthcare costs and higher risks of forthcoming complications.

Fosfomycin is an alternative antibiotic treatment for the stepdown treatment of FUTI [8, 9]. Fosfomycin is a phosphoenolpyruvate analogue and orally available as Fosfomycin-Trometamol (FT). It has been used extensively for uncomplicated cystitis in women, has a good safety profile [10] and possesses a suitable pharmacokinetic profile in healthy volunteers.

In the FORECAST trial (FOsfomycin Randomized controlled trial for *E.coli* urinary tract infections as Alternative Stepdown Treatment), we will investigate the efficacy of FT when used as stepdown therapy of FUTI in women.

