### Participants

#### Inclusion criteria

Competent women (≥18 years), that are hospitalized for the presumed diagnosis FUTI and receive appropriate empirical intravenous antibiotics for ≥48 - ≤120 h, who are judged to be eligible for an intravenous-oral switch by the attending physician, according to the Dutch guideline, that recommends to switch therapy until the patient has been afebrile for 24–48 h and symptoms have improved [2]. Urine (≥10^4^ CFU/ml) or blood culture must reveal *E.coli*, susceptible to both CPX and fosfomycin. A patient is not eligible if non-E.*coli*-type Enterobacteriaceae are present in urine culture (≥10^3^ CFU/ml) or blood culture.

FUTI is defined as UTI with at least one forthcoming systemic symptom or sign and one local symptom at presentation. Local symptoms are dysuria, urinary urgency, urinary frequency, suprapubic/pelvic discomfort, macroscopic hematuria, new urinary incontinence or worsening of pre-existing incontinence, lower abdominal pain, low back pain, flank pain, costo-vertebral angle pain or tenderness on physical examination. Systemic symptoms or signs are fever (≥38.0 C ͦ) or low temperature (< 36 C ͦ), rigors, delirium, hemodynamic instability as a result of sepsis requiring intravenous fluids or an increase in CRP (≥30 mg/L) or leucocytes (≥12*10^9^/L). Local symptoms are not required in case the urine and blood culture yield are positive for a phenotypically identical matched E.coli and UTI is the presumed source of infection according to the treating physician.

Adequate empirical intravenous treatment may consist of amoxicillin+/−clavulanic acid, 2nd or 3rd generation cephalosporin, aminoglycoside, carbapenem, fluoroquinolones, trimethoprim-sulfamethoxazole or a combination and in vitro susceptibility of the causative *E.coli* to at least one of the used agents.

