### Treatment

Participants will be randomized for an intravenous-oral antibiotic switch to either FT 3000 mg every 24 h or CPX 500 mg every 12 h [1]. CPX is chosen for the control group, because most evidence exists for CPX as an oral treatment of FUTI [12, 13]. A double-dummy design is chosen as it is impossible to equalize fosfomycin granules to any form of CPX. An identical placebo will be used for both active substances. All medicines will be manufactured according to Good Manufacturing Principles by the pharmaceutical company Basic Pharma BV, the Netherlands. The duration of total antibiotic therapy is 10 days for all participants, of which 2–5 days empirical intravenous antibiotics and the remaining 5–8 days stepdown therapy with FT or CPX.

FT will be dosed 3 g every 24 h, which is based on a review of the scientific data and expert opinion on the treatment of FUTI and the pharmacokinetics of FT that was available at the moment the study was designed (May 2017). The use of FT every 24 h for more than a single dose was tolerated well in retrospective studies and according to personal off-label use [14]. We do not expect negative effects of accumulation as fosfomycin is registered for intravenous use in dosages as high as 24 g per 24 h [15]. A medication diary needs to be filled by the participant in order to improve medication adherence. All patients receive oral and written information on the trial, including possible risks of participating. Additionally, patients receive a medication folder with instructions for use, contra-indications, interactions and adverse events of both FT and CPX (probable, possible and seldom adverse events). For questions or concerns, participants could contact the local or principle investigator or an independent expert physician.

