### Data collection

In each hospital, authorized and qualified clinical investigators and research nurses will obtain informed consent for participation. Demographic, clinical and microbiological data will be collected and stored for at least 15 years. Data will be collected from questionnaires and supplemented with data from the electronic medical record, see Table 1.

**Table 1 Tab1:** Enrolment, interventions and assessments in the FORECAST study

	Patient identification	Before randomization	Study treatment (5–8 days)	6–10 days post-end of treatment	30–35 days post-end of treatment
Enrolment:					
Screening for eligibility	x				
Entry criteria		x			
Informed consent		x			
Interventions:					
Venapunction^a^		x			
Urine/blood culture	x			x (urine)	
Study treatment			x		
Assessments:					
Electronic patient file		x		x	x
Patient questionnaire		x		x	x
Hand in study diary and residual study medicines				x	

^a^in case of doubt about the following exclusion criteria: pregnancy, neutropenia or renal insufficiency

All participating microbiological and clinical chemistry laboratories are accredited by the Dutch foundation for the promotion of the quality and the accreditation of laboratories in health care (ISO). Susceptibility to fosfomycin and CPX is tested using validated local susceptibility methods, following the European Committee on Antimicrobial Susceptibility (EUCAST) recommendations. The clinical (*E. coli*) isolates will be stored for additional susceptibility measurements, i.e. agar dilution for fosfomycin susceptibility, and molecular analysis.

The primary and secondary endpoints will be collected 6–10 days post-end-of-treatment during a visit and 30–35 days post-end-of-treatment by telephone. Data will be entered into the Case Report Form (CRF) pseudo-anonymously in each participating centre using an unique participant code. The data will be processed by the data management program ‘ResearchOnline’. All steps of the data process will be stored to be able to check validity and plausibility.

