### Endpoints

The primary endpoint is clinical cure (resolution of symptoms) 6–10 days post end-of-treatment. Definitions and criteria of primary and secondary endpoints are described in Table 2.

**Table 2 Tab2:** Endpoints, provided with definitions and a time frame

Endpoint	Definition	Time frame
Clinical cure	Alive with reduction of all initial local and systemic FUTI related symptoms and without additional systemic antibiotic therapy for UTI (except antibiotic prophylaxis)	6–10 days post-end of-treatment (PET) + 30–35 days PET
Microbiological cure	Negative urine culture for E.coli (< 10^3^ CFU/ml), phenotypically identifiable to the initial culture (assessment by microbiologist) ^a^	6–10 days PET
Acquired resistance	Resistance to ciprofloxacin, fosfomycin or new ESBL-producing bacteria in phenotypically identical strain	6–10 days PET
Mortality	-Mortality for any reason	Within 30–35 days PET
	-Mortality related to UTI or study medicines	
ICU admission	-ICU admission for any reason	Within 30–35 days PET
	-ICU admission related to UTI or study medicines	
Readmission	-Readmission for any reason	Within 30–35 days PET
	-Readmission related to UTI or study medicines	
Relapse	Development of new symptoms of UTI after previous clinical and microbiological cure with a phenotypically identical strain as isolated during the initial blood or urine (≥10^3^) cultures.	Within 30–35 days PET
Reinfection	Same definition as relapse, but with phenotypically different strains isolated in cultures (urine, ≥10^3^)	Within 30–35 days PET
Additional antibiotic use	Additional systemic antibiotic therapy for UTI (except antibiotic prophylaxis)	Within 30–35 days PET
Length of hospital stay	-Total days of hospital stay	Within 30–35 days PET
	-Total days of ICU stay	
Days of absenteeism	Converted to full work days:	Within 30–35 PET
	-Paid work	
	-Voluntary work	
Adverse events	Possible or probable related to study protocol	Within 30–35 days PET
Early study medicine discontinuation	Early study medicine discontinuation:	–
	-because of intolerance/adverse events	
	-because of clinical failure	
	-because of resolution of symptoms	

^a^Other strains in urine culture will be reported, but do not fall within this definition

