#### Statistical methods

For the primary endpoint, the difference between the study arm and standard of care (*p* < 0.05) will be calculated with a two-sided Z-score for proportions. Secondary outcomes will be analysed using the following tests: two-tailed Z-score for proportions (p < 0.05), t-test, chi-square, logistic regression, when appropriate.

Linear and logistic regression will be used to identify associations between patient, disease and treatment characteristics) with both study arms with regard to the primary and secondary endpoints. Clinical cure 6–10 and 30–35 days post-treatment in specific subgroups will be investigated in exploratory analyses, based on host or disease characteristics, e.g. age, BMI, Charlson index, use of immunosuppressive drugs, presence of host factors, presence of a short term indwelling catheter, creatinine clearance, diabetes mellitus, days of empirical intravenous antibiotics, class of empirical intravenous antibiotics, and concomitant bacteraemia.

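### Acquired resistance is defined as one undivided endpoint that contains both randomised drugs, so drug-specific effects can offset each other between arms; report the three components separately

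*Protocol article*

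**What the plan says.** The Endpoints section refers the reader to Table 2 for the definitions. There, acquired resistance has one row, assessed 6–10 days after the end of treatment: "Resistance to ciprofloxacin, fosfomycin or new ESBL-producing bacteria in phenotypically identical strain". The row has no sub-items. Other rows in the same table do: mortality, ICU admission, readmission, length of stay, absenteeism and early discontinuation are each divided by dashes, for example with a separate line for "Mortality related to UTI or study medicines".

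Three other places bear on how the row works:

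- Treatment: "Participants will be randomized for an intravenous-oral antibiotic switch to either FT 3000 mg every 24 h or CPX 500 mg every 12 h". Each randomised drug is thus also a component of the endpoint.
- Inclusion criteria: the *E. coli* must be "susceptible to both CPX and fosfomycin", so later resistance to either drug in the same strain is new.
- Data collection: "Susceptibility to fosfomycin and CPX is tested using validated local susceptibility methods". In Table 1 the line "Urine/blood culture" shows urine at 6–10 days as the only follow-up culture.

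The Statistical methods section does not name acquired resistance. It covers it only through a general sentence, "Secondary outcomes will be analysed using the following tests", followed by a list of standard tests to be used as appropriate.

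**The concern.** An either-or endpoint is easy to read when its components are expected to move the same way. Here they are not. Selection by ciprofloxacin would raise the first component in the CPX arm, and selection by fosfomycin would raise the second in the FT arm. The proportion with any of the three adds the components within each arm, so the contrast between arms subtracts one drug's effect from the other's.

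Two readings are then at risk. A small or null difference in the total could be taken as equal selection of resistance when each drug is selecting against itself. A clear difference in the total would not say which drug is losing usefulness.

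The question has some standing in the article itself. The Background notes that "one of the goals of antibiotic stewardship is to reduce fluoroquinolone use because of its selective properties for antibiotic resistance", and the Discussion relies on fosfomycin resistance in *E. coli* being about 1% and stable in the Netherlands. Whether FT leads to less ciprofloxacin resistance, and at what cost in fosfomycin resistance, are two separate questions. The combined row answers neither directly.

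**Working it through.** **The plan's own figure.** The article states no figure for acquired resistance. The number per arm used below is the primary sample size, which reproduces: n = (1.960 + 0.842)² × 2 × 0.925 × 0.075 / 0.10² = 108.9, so 109 per arm, as stated.

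**Why the effects offset.** Let a be the rate of resistance to the drug received, c the rate of resistance to the other study drug and e the rate of new ESBL, with F for the FT arm and C for the CPX arm. If no woman has more than one component, then

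total(FT) − total(CPX) = (a_F − c_C) + (c_F − a_C) + (e_F − e_C).

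The first bracket is the fosfomycin difference, expected positive. The second is the ciprofloxacin difference, expected negative. Their sum is zero only if they are equal in size (and ESBL does not differ); otherwise a net difference remains.

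**Size under assumed rates.** The document gives no resistance rates, so these are illustrations. The inputs are 109 per arm, a two-sided pooled Z-test at 0.05 by exact enumeration, c = 0.5%, no overlap and no ESBL. Differences are FT minus CPX, in percentage points, with the rejection rate in brackets.

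| Own-drug rate, FT / CPX | Total, FT v CPX | Difference in total | Ciprofloxacin resistance alone | Fosfomycin resistance alone |
|---|---|---|---|---|
| 3% / 3% | 3.5% v 3.5% | 0 (4.3%) | −2.5 (25.5%) | +2.5 (25.5%) |
| 5% / 5% | 5.5% v 5.5% | 0 (4.7%) | −4.5 (56.9%) | +4.5 (56.9%) |
| 8% / 8% | 8.5% v 8.5% | 0 (5.3%) | −7.5 (86.3%) | +7.5 (86.3%) |
| 4% / 8% | 4.5% v 8.5% | −4.0 (22.3%) | −7.5 (86.3%) | +3.5 (41.9%) |

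The last row checks against the formula: +3.5 − 7.5 = −4.0. It also shows that the loss does not depend on exact symmetry.

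With c = 1% in place of 0.5%, component power falls to 15.8%, 40.2% and 74.7% for own-drug rates of 3%, 5% and 8%.

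**Where the offset is small.** Take independent components, 0.5% for the other drug and for ESBL, and own-drug rates of 1% (FT) and 10% (CPX). The totals are 1 − 0.99 × 0.995² = 2.0% and 1 − 0.90 × 0.995² = 10.9%. The difference in the total is −8.9 points, against −9.5 for ciprofloxacin alone. Power by the normal approximation is about 77% against 89%. With very unequal selection the total keeps most of the signal.

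**Where events are few.** The event needs the same strain still present in urine at 6–10 days. If the strain persists in 10–20% of women (an assumption), own-drug resistance in 5–8% of all women means that between 5/20 = 25% and 8/10 = 80% of persisting strains have become resistant, which is high. At 2% v 0.5% component power is 10%, and at 1% v 0.5% it is 1.5%, with about 109 × 0.02 = 2.2 and 109 × 0.01 = 1.1 own-drug events.

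**The case against.** A reader might infer that the two drugs' effects cancel out and that the endpoint is uninformative. The article does not support that. Full cancellation needs equal own-drug rates; the document gives none, and with unequal rates a net difference stays visible.

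A reader might also infer that only the combined proportion will be analysed. That is not stated either. Table 2 is a table of definitions, the tests in Statistical methods are generic, and nothing rules out reporting by component. The full protocol or SAP may provide it. The missing dashes are weak evidence of intent: adverse events also have a single row, and nobody would conclude that event types will go unreported. What remains is that the article sends the reader to Table 2 for the definition, and the endpoint defined there is one that nets opposing effects if it is compared as written.

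Nor is sparing fluoroquinolones the trial's rationale. It takes one sentence in the Background. The main case is the shrinking choice of oral stepdown drugs, and the objective is non-inferiority on clinical cure. Acquired resistance is absent from the secondary endpoints listed in the Abstract and the Discussion. This limits the weight of the point but leaves the row's definition unchanged.

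Finally, at low rates splitting gives listed counts and no usable test. That stands. It argues for estimates with intervals; pooling components that run in opposite directions does not recover the information.

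**Conclusion.** The point holds as a weakness in how a secondary endpoint is defined. Comparing the arms on the row as written mixes drug-specific effects that are expected to run in opposite directions. They can offset in part, or in full if the own-drug rates are equal, and any remaining difference does not identify the drug concerned.

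The direction rests on one assumption beyond the text: that resistance to a drug arises more often in the arm that received it. The size rests wholly on assumed rates. The loss ranges from almost complete (equal rates) through substantial (22.3% against 86.3% power at 4% and 8%) to minor (about 77% against 89% at 1% and 10%). Because the event requires a persisting strain, the 5–8% scenarios may be optimistic. The benefit of separate reporting is therefore a result that can be interpreted, not a reliable test. The primary endpoint, margin, sample size and non-inferiority decision are untouched.

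**What to change.** In Table 2, divide acquired resistance into three dashed components: resistance to ciprofloxacin, resistance to fosfomycin, and new ESBL production, each in the phenotypically identical strain at 6–10 days after the end of treatment. Report each by arm as counts with a difference and 95% CI. Keep the proportion with any of the three as a descriptive total without a between-arm test. If the full protocol or SAP already reports by component, it is enough to align Table 2 with it.

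The cost is one table row and the matching analysis lines. Susceptibility to both study drugs is already tested, and ESBL status is already needed for the existing definition, so no new data are required. The drawback is three secondary comparisons in place of one, each with few events. The text should say that they are estimates and not powered tests.

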#### Safety

Our entry criteria are designated to reflect daily practice with regard to the safety of the participants. Candidates should be diagnosed with FUTI as the primary reason for hospitalization. All identified uropathogens must be *E. coli* susceptible to both fosfomycin and CPX. Patients should be treated with appropriate intravenous antibiotics for at least 48 h. The attending physician determines the eligibility for the intravenous-to-oral switch. Patients that require more than 5 days of intravenous antibiotics will be excluded as this is considered a complicated course. Our goal is to investigate a representative population by including as many patients as possible, and only exclude extremely vulnerable patients (e.g. non-competent patients, renal transplant recipients, pregnant women), patients that require an alternate antibiotic strategy (e.g. renal abscess, endocarditis) or patients for which other endpoints should be used to estimate efficacy (e.g. men). Adverse events should be actively reported in the medication diary by participants in order to measure tolerability. Furthermore, these will be checked actively with questionnaires at 6–10 days and 30–35 days post-end of treatment. De-blinding is possible 24/7 h in case severe harm could be potentially prevented, and after consultation of the coordinating investigator. Serious adverse events and Suspected unexpected serious adverse reactions (SUSARs) will be reported during follow-up. All participants are automatically insured by a subject and liability insurance.

The study will be monitored by qualified monitors from the University Medical Centre Utrecht. For each participating centre the following procedures will be checked after the first 5 inclusions and thereupon annually: at least 10% of signed Informed Consent forms, in- and exclusion criteria, defined variables including the primary endpoint, source data verification, missed SAE’s, or SUSAR’s.

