An interim analysis will be performed by the Data and Safety Monitoring Board (DSMB) after inclusion of 50 and 100 participants. De-blinded data will be delivered by an independent statistician to the DSMB, which will function as an advisory board, i.e. it will provide non-binding advice to the principal investigator. After inclusion of 50 participants an interim analysis will be performed regarding adverse events, medication adherence and early study medicine discontinuation as a result of adverse events/intolerance. Based on these results, the DSMB could recommend to adjust the dosage of FT. After inclusion of 100 participants, an interim analysis will be performed regarding Serious Adverse Events (SAE’s), early study withdrawal and the primary endpoint. Based on these results, the DSMB could recommend to stop the study, in case the interim analysis shows a probability of finding non-inferiority at the final analysis of less than 5% based on the conditional power (futility) [17] or an unexpected high rate of possible related SAEs or early study withdrawals, in particular in the FT arm (safety).

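### Table 2 limits the adverse-event endpoint to events judged related; a row for all adverse events, compared by arm, should stand beside it

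*Protocol article*

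**What the plan says.** The Endpoints section refers to Table 2 for the definitions of all primary and secondary endpoints. The whole definition in the adverse-event row is "Possible or probable related to study protocol", up to 30–35 days post-end of treatment (PET). No row covers all adverse events.

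Three neighbouring endpoints are handled differently. Mortality has a line "Mortality for any reason" and a second line for deaths related to UTI or study medicines. ICU admission has "ICU admission for any reason" and a related line, and readmission follows the same pattern.

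On collection, the Safety section says: "Adverse events should be actively reported in the medication diary by participants in order to measure tolerability". It adds that "these will be checked actively with questionnaires at 6–10 days and 30–35 days post-end of treatment" and that "Serious adverse events and Suspected unexpected serious adverse reactions (SUSARs) will be reported during follow-up". None of these sentences limits collection to related events.

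The interim plan, also under Safety, reviews adverse events, adherence and early discontinuation for adverse events or intolerance at 50 participants. At 100 it reviews SAEs, early withdrawal and the primary endpoint. Relatedness appears only in the safety ground for advising a stop, an "unexpected high rate of possible related SAEs or early study withdrawals".

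**The concern.** Randomisation with blinding lets the difference in event rates between arms show what the drug does, without anyone judging single cases. An endpoint that admits an event only after a causality judgement gives up part of that advantage. Such judgements recognise known effects more easily than unknown ones, so an unexpected harm could be recorded in the diary, judged unrelated and never reach the comparison.

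This matters here because experience with repeated daily FT is limited. The Treatment section says that it was "tolerated well in retrospective studies and according to personal off-label use". The Discussion adds one healthy-volunteer study without placebo, with a diarrhoea signal on daily dosing, and says its bearing on these participants is unknown. Measuring tolerability is the stated purpose of the diary.

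A smaller problem is the reference point. The adverse-event row speaks of the study protocol, while the other related rows speak of UTI or study medicines. What an event must be related to is therefore unclear.

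**Working it through.** **1. The plan's own figure.** The documents give no adverse-event rate and no power for this endpoint. The only sample-size figure concerns the primary endpoint: 2 × 0.925 × 0.075 × (1.960 + 0.842)² / 0.10² = 108.9, so 109 per group, as stated. Then 218 × 1.1 = 239.8, so 240 in total. Neither figure depends on how adverse events are defined.

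**2. Table 2 side by side.**

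| Endpoint | Any cause | Related |
|---|---|---|
| Mortality | yes | yes, to UTI or study medicines |
| ICU admission | yes | yes, to UTI or study medicines |
| Readmission | yes | yes, to UTI or study medicines |
| Adverse events | no | yes, to study protocol |

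**3. What the filter does to power (illustration).** From the documents: 240 / 2 = 120 per arm and two-sided 5%. Assumed, because the documents give no rates: risk of an adverse event 10% on CPX and 25% on FT; half of background events judged related; a share b of the excess FT events judged related.

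Related-event risks are p1 = 0.10 × 0.5 = 0.05 on CPX and p2 = 0.05 + 0.15b on FT.

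Power = Φ[(d − 1.96·s0) / s1], where d = p2 − p1, s0 = √(2·p̄(1 − p̄)/n), s1 = √((p1(1 − p1) + p2(1 − p2))/n) and p̄ is the mean of p1 and p2.

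- All events counted: d = 0.15, p̄ = 0.175, s0 = 0.04905, s1 = 0.04809. Power = Φ[(0.15 − 0.09614)/0.04809] = Φ(1.12) = 87%.
- Related events, b = 0.5: p2 = 0.125, d = 0.075, s0 = 0.03648, s1 = 0.03616. Power = Φ[(0.075 − 0.07150)/0.03616] = Φ(0.10) = 54%.

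| Share of excess judged related | Related-event risks, FT v CPX | Power |
|---|---|---|
| 100% | 20% v 5% | 94% |
| 80% | 17% v 5% | 85% |
| 50% | 12.5% v 5% | 54% |
| 30% | 9.5% v 5% | 27% |
| 0% | 5% v 5% | 2.5% (chance only) |
| *All events counted* | *25% v 10%* | *87%* |

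**4. Other assumed rates, same attribution.** With 35% v 20%, power is 74% for all events, and 87%, 39% and 18% for related events at b = 100%, 50% and 30%. With 15% v 5%, it is 74% for all events, and 84%, 43% and 22%. The pattern is the same: a modest gain if the harm is fully recognised and a large loss if it is not.

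**The case against.** **The filter can help.** A causality judgement that discards background events sharpens the comparison. In the table above it raises power from 87% to 94% when all of the excess is recognised. With 90% of the excess and half of background judged related, power is 91%; with 80% of the excess and 30% of background it is also 91%. A reader might infer that blinded attribution can only remove true events or add noise, or that the filter always costs power. The figures do not support either reading. The known signal, diarrhoea on daily dosing, may well be judged at least possibly related. This objection stands, and it is a reason to keep the related row, though not as the only row.

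**Serious harm is covered elsewhere.** Death, ICU admission and readmission are compared for any reason, hospital and ICU days are counted in total, SAEs are reported, and discontinuation for intolerance or adverse events is a separate endpoint. This also stands, and it narrows the gap mainly to non-serious events, plus serious ones that lead to none of those outcomes.

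**The interim looks are not filtered.** A reader might infer that the 50-participant look, after which the DSMB could recommend a change to FT dosing, rests on the related-only endpoint. The text says adverse events without qualification, and the 100-participant look likewise covers SAEs without one. Only the wording of the stop ground is restricted, and the DSMB's advice is non-binding.

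**The evidence for daily FT is wider than retrospective and off-label use.** The Treatment section also cites a review of scientific data, expert opinion and high intravenous dosages. That is correct, but it does not make attribution a safe gatekeeper for unexpected events.

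**A condensed article leaves tables to fuller documents.** This does not answer the point. The endpoint definition is not omitted here; it is stated, and an analysis plan that follows it would compare related events only.

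**Conclusion.** The point holds in a limited form. Table 2 makes the adverse-event comparison depend on attribution, departs from the pattern it sets for three other endpoints, and leaves the object of relatedness unclear. The exposure is lost sensitivity to unrecognised, mainly non-serious, harm. A reader might infer bias towards one arm, but blinding should keep the judgement from differing by known allocation, and nothing in the document suggests otherwise.

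The size depends on attribution. Under the assumed 25% v 10% with half of background events judged related, power under the filter runs from 94% down to 27% when 30% of the excess is attributed, and to chance when none is, against 87% for all events. These rates and shares are assumptions, so the figures show direction and range and do not predict this trial's power. The primary analysis, 109 per group and 240 in total are unaffected. Since no filter is stated at collection, nothing need be lost if the definition is corrected. The change should be made: it is cheap and improves a stated endpoint.

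**What to change.** In Table 2, replace the single adverse-event row with two, both compared by arm:

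1. all adverse events from first study dose to 30–35 days PET, regardless of judged causality;
2. adverse events possibly or probably related, stating whether this means related to study medicines or to study protocol.

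In the interim paragraph under Safety, align the wording of the safety ground with the review of all SAEs by arm that the same paragraph already describes, with related SAEs shown as a subset.

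The cost is wording and some tabulation. As described, the diary and questionnaires already supply the data. The downside is slightly longer tables that include background events.
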